### Statistical analyses

This trial aims to examine whether MOGBA (a) improves children’s movement competence (Dragon Challenge); (b) increases MVPA during PE lessons (acceleromters), (c) reduces sedentary time both in school and outside of school (accelerometers) (d), improves physical fitness (plank and standing long jump), (e) improves self-perceptions of game and physical competence (Game Play Perception Profile). We hypothesize that children in the MOGBA intervention, compared to those in the control group, will display more favorable changes in these variables identified above.

Statistical analyses of the primary and secondary outcomes will be conducted with linear mixed models using IBM PASW Statistics 25 (SPSS Inc. Chicago, IL) software. Impacts are estimated using an intention-to-treat (ITT) approach, with alpha levels set at p < 0.05. Linear mixed models will be fitted to compare continuous outcomes. Group, time, and group-by-time interaction will be assessed as fixed effects within the model, with covariates of gender and year level also included as fixed effects. The school a student belongs to and the research site will be included as a random intercepts within the model to account for the multi-level nature of the data, and subject (student ID) will be included as a random intercept to model repeated measures at the individual level. Differences of means and 95% confidence intervals (CIs) will be determined using the linear mixed models. If the variables used for secondary outcomes (questionnaires) fail tests of multivariate normality, non-parametric methods will be utilised, or the variables for use in the linear models will be an individual’s factor score from a confirmatory factor analysis of the scales with the appropriate estimator chosen given the non/normal nature of the data.

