### Trial design

A cluster randomized control trial will be used to assess the effectiveness of MOGBA in a school setting, as this is perceived to be an ideal setting for the promotion of movement competence and PA [22]. Another potential option available was to establish the trial within MTP programs, as clusters. It was felt that, due to the eclectic and disparate nature of these programs, controlling and accounting for the variability both within intervention and control groups would be more problematic than a school setting. It is intended to use the findings of this trial to inform the scalability of MOGBA across MTP programs.

Through the trial we aim to examine whether MOGBA (a) improves children’s movement competence; (b) increases Moderate to Vigorous Physical Activity (MVPA during PE lessons, (c) increases MVPA time in school (d), improves physical fitness, (e) improves self-perceptions of game and physical competence. We hypothesize that children in the MOGBA intervention, compared to those in the control group, will display more favorable changes in movement competence, physical activity, physical fitness, physical self-perceptions and game perceptions.

The 9-week intervention will be delivered during the school day and target children in the school years containing the age ranges 8/9, 9/10, 10/11, 11/12 years. Baseline measures, including all primary and secondary outcomes, will be taken prior to the commencement of the intervention, which will be staggered across the sites to prevent clashes with key educational milestones within the respective countries. This is a deviation from the original study protocol in which there was originally 4 sites, including the USA, which was subsequently reduced to 3 sites as a result of Covid-19 restrictions on accessing schools. After baseline measures are taken, schools will be randomly allocated into either an intervention or wait-list control group. Schools allocated to the experimental group will be assigned a facilitator to deliver the 14 MOGBA activities across a 9-week period.

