By contrast, the wait-list control group undertakes the standard content planned by their teachers across the intervention period. This content will vary from country to country and will also be subject to change based on the seasonality of delivery across the RCT. As each site has its own control group, it is not expected that heterogeneity among the countries will introduce bias. Additionally, as the countries involved have relatively similar physical education programs expressed through the development of movement skills with transference into game and sport based activities, the differences related to individual sites is likely minimal. All countries will follow some sort of Physical Education curriculum, whether that is determined at national, provincial or regional level. All primary and secondary outcomes will be assessed at 3-month post-test with the exception of in-school physical activity, which will be assessed between weeks 7–9 of the intervention period to assess the impact of the program on student in-school MVPA. Schools from the wait-list control group will receive the MOGBA program after the completion of post-test assessments.

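### The group, time and group-by-time model leaves the baseline difference between arms free although schools are randomised after baseline; the effect is unbiased but estimated less precisely than it could be, by an amount the article does not allow one to fix.

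*Protocol article*

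**What the plan says.** The Statistical analyses section of the protocol article specifies linear mixed models: "Group, time, and group-by-time interaction will be assessed as fixed effects within the model". The only covariates it lists are gender and year level. The random part is given as "The school a student belongs to and the research site will be included as a random intercepts within the model", and "subject (student ID) will be included as a random intercept to model repeated measures at the individual level". The hypothesis is worded in terms of change: the intervention children "will display more favorable changes in these variables identified above". The baseline score is thus one of the repeated outcomes. It is not a covariate, and its mean is not held equal between the arms.

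The Trial design section fixes the order of events: "Baseline measures, including all primary and secondary outcomes, will be taken prior to the commencement of the intervention", and "After baseline measures are taken, schools will be randomly allocated into either an intervention or wait-list control group". The Randomization section repeats that order and adds pairing of schools on a socio-economic rank within schooling level at each site. Follow-up is a single occasion: "All primary and secondary outcomes will be assessed at 3-month post-test", except in-school physical activity, which is measured once in weeks 7–9. Every outcome therefore has two time points.

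**The concern.** With two time points, complete data and random intercepts, the group-by-time coefficient equals the difference between arms in mean change. Taking a change score subtracts the whole observed baseline difference from the post-test difference. Because allocation follows baseline, that baseline difference is pure chance, and subtracting all of it is the best choice only if school means are perfectly correlated over time. Otherwise a smaller multiple should be subtracted.

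What is at stake is precision on the primary outcome and all secondary outcomes, in a trial whose effective sample is 36 schools. Bias and validity are not at stake.

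**Working it through.** **Inputs from the Sample size calculation section.** d = 0.4, 80% power, alpha 0.05, m = 25 children per school, ICC = 0.20, correction factor 5.8, 36 schools (18 per arm). The abstract's eight schools at each of three sites would make 24; I use the 36 on which the calculation rests.

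**The plan's own figure.** 1 + 24 × 0.20 = 5.8. A one-sided alpha of 0.05 gives 78 per arm, so 156 children; 156 × 5.8 = 904.8, and 904.8 / 25 = 36.2 schools. This reproduces the plan. A two-sided alpha gives 99 per arm, and 198 × 5.8 = 1,148 children (about 46 schools), which does not. Sidedness is a separate matter. For this point, what counts is that the calculation takes no credit for baseline data and gives no baseline to follow-up correlation.

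**Inputs that must be assumed.** CAC is the correlation over time of the school effects. IAC is the correlation over time of children's scores within school. The article gives neither. They combine into the correlation of school means:

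r = [m × ICC × CAC + (1 − ICC) × IAC] / [1 + (m − 1) × ICC] = (5 × CAC + 0.8 × IAC) / 5.8

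**Variance of the arm difference, relative to post-test only.** The change score has 2(1 − r). The best use of baseline has 1 − r². Their ratio is (1 − r²) / [2(1 − r)] = (1 + r)/2, so the ideal saving is (1 − r)/2. For IAC from 0.3 to 0.9:

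| CAC | r | ideal saving |
|---|---|---|
| 1.0 | 0.90–0.99 | 1–5% |
| 0.9 | 0.82–0.90 | 5–9% |
| 0.8 | 0.73–0.81 | 9–13% |
| 0.6 | 0.56–0.64 | 18–22% |

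Estimating the slope costs a little. In simulation, ideal savings of 25%, 11% and 6% (r = 0.5, 0.77, 0.87) became 21%, 8% and 3%.

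**Power, two-sided 0.05, d = 0.4, 36 schools.** With total variance 1, a school mean has variance 0.20 + 0.80/25 = 0.232. The post-test-only standard error is √(4 × 0.232 / 36) = 0.161, and each method multiplies it by the root of its factor above. Using the noncentral t (34 df; 33 with a baseline slope), post-test only gives 68%.

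| r | change score | best use of baseline |
|---|---|---|
| 0.4 | 60% | 75% |
| 0.5 | 68% | 80% |
| 0.6 | 77% | 86% |
| 0.77 | 95% | 97% |
| 0.87 | 99.7% | 99.8% |

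The right-hand column assumes the ideal slope, so it is slightly optimistic.

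**Which remedy delivers the gain.** Two checks matter.

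- *Dropping the group main effect alone.* With only constant school intercepts, the fitted model implies a baseline slope of about 0.86–0.95 whatever the true r. At CAC 0.6 and IAC 0.5, r = (3.0 + 0.4)/5.8 = 0.586. A slope of 0.90 gives 1 + 0.81 − 2 × 0.90 × 0.586 = 0.755, against 2 × 0.414 = 0.828 for change: a ratio of 0.91. The ideal ratio is (1 + 0.586)/2 = 0.79. At r = 0.4, power would rise only from 60% to about 65%. A school-by-time random effect is needed for the baseline to be weighted properly.
- *Regressing post-test on baseline (ANCOVA).* Simulated variance relative to change, at IAC 0.5 and 0.8:

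| CAC | child's baseline only | child's and school-mean baseline |
|---|---|---|
| 1.0 | 2.17, 1.38 | 1.00, 1.04 |
| 0.8 | 1.05, 0.92 | 0.93, 0.95 |
| 0.6 | 0.86, 0.84 | 0.87, 0.81 |

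The child's own baseline alone can be clearly worse than the planned model.

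**The case against.** The strongest reply is that nothing here is an error. The planned contrast answers the hypothesis as worded, is unbiased, and does not conflict with a sample size that ignores baseline. All of that stands.

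A second reply is that the gain rests on correlations the article does not report and may be trivial. That also stands: at r = 0.87 power is above 99% either way, and if school effects are fully stable, as the planned constant school intercept supposes, at most 1–5% of the variance can be saved. Third, pairing schools on socio-economic rank may already reduce chance baseline imbalance. The figures above ignore pairing, so they may overstate the gain. Fourth, the planned mixed model can use children with only one of the two measurements, which ANCOVA drops unless values are imputed. This counts against ANCOVA but not against the common-baseline mixed model.

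A reader might infer from the first row of the power table that the planned estimator is worse than ignoring baseline. That needs r below 0.5, hence a school-level correlation of about 0.5 or less over one short follow-up. Nothing in the article supports such a value, and it should be treated as an extreme. A reader might equally infer that any baseline adjustment would beat the plan; the simulation with the child's baseline alone shows otherwise.

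What survives is the direction: allocation follows baseline, so a common baseline mean is justified by design and, with the baseline properly weighted, costs nothing in large samples.

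**Conclusion.** The point holds as a recommendation on efficiency. The article fixes an estimator that leaves free a baseline difference whose expectation is zero by design. Confidence in the direction is high. Confidence in the size is moderate at best, because it depends on r: about 20% of the variance at r = 0.6, 11% at 0.77, 6% at 0.87, and slightly less once the slope is estimated. These figures assume m = 25, ICC 0.20, 36 schools, complete data and no benefit from pairing. The documents do not support calling the analysis biased or invalid, or saying that this choice undermines the stated sample size.

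**What to change.** In the Statistical analyses section, state that the effect is the arm difference at post-test from the repeated-measures model with the group main effect removed, so that both arms share one baseline mean, and with a school-by-time random effect added. Keep gender, year level and the school, site and student terms. This form still uses children with one missing measurement.

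A similar but not identical alternative is to regress the post-test score on both the child's baseline and the school-mean baseline, with the same other covariates and the school and site terms. It should not use the child's baseline alone. It can lose slightly (0–4% in the simulations) when school means are almost perfectly correlated over time, and it drops children who lack either score unless they are imputed.

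The cost is a sentence or two of text and a small change in model syntax, with no new data and no extra participants. Fixing the choice in advance also removes any later choice between change-score and adjusted results.

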### Sample size calculation

A sample size calculation was completed to estimate the number of schools needed for the trial. Sampling for a two-group clustered RCT is developed around data from previous clustered trials assessing game skill (e.g., support, decision-making and defence) and fundamental movement skill (e.g., throw, kick, under-arm throw and catch) development [23, 24]. The lowest effects in these trails were observed for the fundamental movement skill of catch (effect *d* = 0.4), and the game skill of decision making (*d* = 0.4).

Without accounting for clustering among schools (schools being alike and reducing the power of data), approximately 156 students are required to detect an effect of d = 0.4 at 80% power with alpha 0.05. To adjust for clustering, the following correction factor is applied (1+ (m– 1) x ICC) [25], where m = students per school and ICC = the intra-class correlation coefficient (between school variance / between school variance + within school variance). Assumptions are based on clustering at the school level (one class recruited per school, with ~25 students per class), and a conservative ICC of 0.20 based on data from a school based intervention [22], resulting in a correction factor of 5.8. The resulting student sample is ~904 students at 36 schools (18 intervention, 18 control).

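### The primary mixed model has no school-by-time random effect, so in this school-randomised trial the group-by-time test is not protected against school-level variation in change

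*Protocol article*

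**What the plan says.** The Statistical analyses section sets out the linear mixed model for the primary and secondary outcomes.

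- Fixed part: "Group, time, and group-by-time interaction will be assessed as fixed effects within the model", with gender and year level as covariates.
- Random part: "The school a student belongs to and the research site will be included as a random intercepts within the model", and "subject (student ID) will be included as a random intercept to model repeated measures at the individual level".
- Test level: "with alpha levels set at p < 0.05", with 95% CIs from the same model.

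The hypothesis concerns more favourable change under MOGBA than under control, so group-by-time is the treatment test. The Trial design section gives the primary outcome two measurements, baseline and the 3-month post-test. The Randomization section allocates whole schools, in ranked pairs within site and schooling level. The Sample size calculation section assumes "one class recruited per school, with ~25 students per class" and "a conservative ICC of 0.20 based on data from a school based intervention", and arrives at 36 schools.

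The article mentions no school-by-time effect, random slope for time, cluster-robust variance or school-level analysis.

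**The concern.** When schools are randomised, the error term for the treatment effect must include the variation between schools in the quantity being compared. Here that quantity is change. A school intercept that is the same at both time points describes how schools differ in level and says nothing about how they differ in change. The model therefore assumes that, apart from the treatment effect, every school has the same true change.

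The article itself gives reasons to doubt this. The Introduction says that skill acquisition depends on conditions that teachers and coaches create. The Trial design section leaves control content to each school's teachers and expects it to vary.

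If true change does vary between schools, the standard error is too small and the degrees of freedom too many. This affects the primary outcome and every secondary outcome analysed with the same model. The results are meant to inform wider use of MOGBA across Made to Play programs.

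**Working it through.** **1. The plan's own figures.** The design effect is 1 + (25 − 1) × 0.20 = 5.8, as stated ("resulting in a correction factor of 5.8"). Then 156 × 5.8 = 904.8 students, and 904.8 / 25 = 36.2 schools. These match the stated ~904 and 36. The ICC of 0.20 enters here as an ICC of scores.

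**2. What the planned test does.** For child *i* in school *k*, the post-test minus baseline difference removes the site, school and student intercepts and the gender and year-level main effects. Only the residual remains. With balanced, complete data the group-by-time test is thus a two-sample t-test on individual change, with 36 × 25 − 2 = 898 degrees of freedom. A test on school mean changes has 36 − 2 = 34.

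This was checked by fitting the model with school and student intercepts to three simulated data sets. The test statistics were 1.2932, 1.2846 and 0.8660, and the t-test on change gave the same values to four decimals.

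**3. Size of the error.** Inputs from the Sample size calculation section: m = 25, ICC = 0.20. Assumed, because the documents do not give them:

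- CAC, the correlation of true school effects between the two time points
- s, the within-school correlation of a child's scores over time, 0.5 to 0.8
- no correlation of change within pairs or sites
- a two-sided 5% test

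Formulas:

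- ICC of change = 0.20(1 − CAC) / [0.20(1 − CAC) + 0.80(1 − s)]
- Design effect of change, D = 1 + 24 × ICC of change
- True SE / planned SE = √D
- Type I error = 2[1 − Φ(1.96/√D)]

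Example, CAC 0.90 and s = 0.5: ICC of change = 0.02/0.42 = 0.048; D = 2.14; √D = 1.46; type I error = 18%.

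| CAC | ICC of change | D | SE understated by a factor of | Type I error |
|---|---|---|---|---|
| 1.00 | 0 | 1.00 | 1.0 | 5% |
| 0.95 | 0.024–0.059 | 1.59–2.41 | 1.3–1.6 | 12–21% |
| 0.90 | 0.048–0.111 | 2.14–3.67 | 1.5–1.9 | 18–31% |
| 0.80 | 0.091–0.200 | 3.18–5.80 | 1.8–2.4 | 27–42% |

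Each range runs from s = 0.5 to s = 0.8.

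**4. Simulation.** With 36 schools of 25, ICC 0.20, s = 0.7 and 8,000 trials per setting, the planned test rejected a true null in 4.9%, 10.3%, 16.4%, 24.0% and 34.9% of trials at CAC 1.0, 0.98, 0.95, 0.90 and 0.80. A t-test on school mean changes rejected in 4.7% to 5.2% of the same settings.

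**5. Sensitivity.** At CAC 0.90 and s from 0.5 to 0.8, the closed form gives 11–19% if the ICC is 0.10 and 8–12% if it is 0.05. The abstract implies 24 schools instead of 36. With about 38 children per school, CAC 0.80 and s = 0.7, the simulated error was 44%, against 35% with 36 schools.

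**The case against.** **The inflation is not a known quantity.** This stands. The documents give neither CAC nor an ICC of change, and the plan calls its ICC of 0.20 conservative. A reader might infer that type I error is several times 5% as a matter of fact. The documents do not support that: at CAC 1.0 it is 5%, and with a small ICC the inflation is modest.

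**The 5.8 is not the inflation that the test leaves out.** A reader might set a 5.8-fold allowance in the sample size against none in the analysis. But 5.8 applies to scores, while the tested quantity is change, whose ICC is generally different. At CAC 0.90 and s = 0.7 it is 0.02/(0.02 + 0.24) = 0.077, which gives D of about 2.8. The article states no ICC of change, so 42% cannot be called the error under the plan's own design effect.

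**The design removes some of the variation.** Schools are paired within site and level, each site has its own controls, and the start is staggered by site. Change shared within a pair or site balances across arms and does not inflate the error. The figures above ignore this, and its size is unknown. University-affiliated facilitators, not class teachers, deliver MOGBA, which weakens the teacher argument in that arm.

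**The rates are two-sided.** False claims of benefit are half of them: about 6–10% at CAC 0.95 and 9–15% at 0.90, against a nominal 2.5%.

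**It might be left to a fuller document.** This does not stand. The article lists the random effects and says that school and site serve to handle the multilevel structure. For the tested contrast they do not.

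**Conclusion.** The point holds for the structure of the model and needs no numerical assumption there. The stated random effects drop out of the treatment contrast, so the planned standard error carries no allowance for school-level variation in change, although schools are the randomised units. The p-value and 95% CI are valid only if true school effects are fixed over time; observed school means may still differ through child-level error. Otherwise they are anti-conservative.

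How far is conditional. Under the assumptions in the check, a CAC of 0.95 already at least doubles the nominal 5%. A smaller ICC, or change shared within pairs or sites, reduces the inflation. The error affects the primary analysis and the correction is simple, so it should be made before the analysis is run.

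**What to change.** Add a school-by-time random effect (a random intercept for school within each time point) to the primary model and to every secondary outcome model of the same form. Test group-by-time with Satterthwaite degrees of freedom. Satterthwaite without the added term would not help, because the fitted model would still place all error in change at student level.

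A follow-up model with baseline as covariate, group as fixed effect and school as random intercept is a valid alternative, but it is a different estimator, and no general precision gain should be claimed for it. For example, take s = 0.5 and fix the baseline slope at its within-school value of 0.5. The variance of a school mean is 0.20 + 0.80/25 = 0.232.

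- At CAC 0.90 the covariance over time is 0.18 + 0.016 = 0.196. The school-level variance is 0.232 × 1.25 − 0.196 = 0.094 with baseline adjustment, against 2(0.232 − 0.196) = 0.072 for change.
- At CAC 0.50 the covariance is 0.116, and the order reverses: 0.174 against 0.232.

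The cost is one line in the analysis section and in the model syntax. Confidence intervals become wider but correct, and no new data are needed.

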#### Game and physical self-perceptions

An individual’s levels of perceived and actual physical competence have differing effects on their levels of motivation in a physical domain. Among children, perceived competence appears to affect motivation towards PA more than actual competence [50], and perceived competence appears to mediate the relationship between actual motor skill competence and PA levels [51, 52].

Children in most countries are exposed to increasing levels of game play and team sports as part of the school curriculum from ages 9–12 years. Given the positive relationship between motor-skill competence [7, 46, 53] and game play competence [7], assessment of changes in perceived physical competence and specific game-play competence appear relevant within an intervention designed to improve both.

The Game play perception profile (GPPP) is used to assess self-perception of perceptual-cognitive related game play among upper elementary school children. The GPPP measures two distinct factors using a four-point scale (Strongly Disagree—Strongly Agree): i) game-play perception–five items reflecting ability across game themes, and ii) game self-perception–four items reflecting abilities in relation to others. The instrument displays acceptable item distribution, item total correlations (>.30) and internal reliability (α = .84 & .85). Change in mean (< 5%) and ICC (.81 & .81) indicate the sub-scales display high levels of test-retest reliability, with face validity (proportion of correctly identified question themes) above 80% for all items and sub-scales. The validity of this measure will be further tested in the recruited cohort using confirmatory factor analysis of the underlying factor structure. Children’s physical self-perception will also be measured using an adaptation of Harter’s physical self-perception scale [54]. Six items are framed as either/or statements using a two-point scale on either side of the statement (Really true for me, sort of true for me).

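### A normality test that four-level questionnaire items will almost always fail decides the self-perception analysis, and leads to two alternatives with no rule for choosing and no stated clustering provision for one of them

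*Protocol article*

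**What the plan says.** The default in the protocol article, Statistical analyses, is clear: "Statistical analyses of the primary and secondary outcomes will be conducted with linear mixed models". The fixed effects are group, time and their interaction, with gender and year level as covariates. Clustering is handled inside that model: "The school a student belongs to and the research site will be included as a random intercepts within the model", with a further random intercept for the student. The model is also the stated source of the mean differences and 95% confidence intervals.

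A conditional rule for the questionnaires follows. It takes effect when their variables "fail tests of multivariate normality, non-parametric methods will be utilised". As a second option, the same sentence lets each child's CFA factor score serve as the outcome in the mixed models. How that factor analysis is to be estimated is left to the data: "with the appropriate estimator chosen given the non/normal nature of the data". The rule names no normality test and no non-parametric method. It does not say whether items, scale scores or residuals are tested. The two alternatives are joined by a bare 'or'.

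The instruments are described under Game and physical self-perceptions. Of the Game Play Perception Profile (GPPP) the section says: "The GPPP measures two distinct factors using a four-point scale". The factors have five and four items. The physical self-perception scale has six either/or items with two points on each side, which makes four ordered levels.

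**The concern.** There are three linked problems.

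1. **The trigger is close to certain.** Four-level responses are discrete, and about 900 children give a normality test very high power. What reads as a fallback will in practice be the analysis.
2. **The trigger looks at the wrong quantity for a mixed model.** A linear mixed model makes assumptions about residuals and random effects, not about the raw variables, and its mean contrasts are robust at this sample size. The gate can set aside a sound cluster-adjusted analysis for no good reason.
3. **What follows the trigger is open.** One route changes the outcome variable and leaves its estimator to be chosen in the light of the data. The other leaves the only model in which the article describes any handling of school. Schools are the unit of randomisation, so a non-parametric method that treated children as independent would understate the uncertainty.

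At stake are the validity and the pre-specification of the game and physical self-perception results, which are among the trial's stated aims.

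**Working it through.** **The plan's own figures.** Sample size calculation gives 156 students before clustering, about 25 per school and an ICC of 0.20. The design effect is 1 + (25 − 1) × 0.20 = 5.8, and 156 × 5.8 = 904.8, which matches the stated ~904 students at 36 schools (18 per arm). The 156 is taken as given here.

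**Step 1: how often would the normality test fail?** The documents give no item distributions, so these are assumed. Items came from a one-factor model with five items (loading 0.78) and four items (loading 0.80), chosen to be close to the GPPP's stated alphas of 0.84 and 0.85. They were cut into four levels at symmetric, mildly skewed or strongly skewed thresholds. Mardia's test was counted as failed if skewness or kurtosis had p < 0.05. There were 150 data sets per setting.

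| Thresholds | N | Five items, Mardia | Two scale scores, Mardia | Shapiro-Wilk, first scale score |
|---|---|---|---|---|
| Symmetric | 904 | 100% | 100% | 100% |
| Mild skew | 904 | 100% | 100% | 100% |
| Strong skew | 904 | 100% | 100% | 100% |
| Symmetric | 450 | 98% | 100% | 100% |
| Mild or strong skew | 450 | 100% | 100% | 100% |

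One qualification applies. For the items at N = 904, a single Mardia component can pass: skewness alone rejected in about 1% of symmetric data sets, and kurtosis alone in about 9% of mildly skewed ones. Near-certain failure holds for the usual joint use of both.

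**Step 2: what would a rank test that ignores school do?** This step is conditional, because the protocol names no such test. With m children per school, a student-level test at nominal two-sided 5% has true type I error of about 2[1 − Φ(1.96 / √(1 + (m − 1) × ICC))]. This was set beside a simulated Mann-Whitney test on a five-item scale score (36 schools of 25, no treatment effect, 2,000 data sets per row).

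| ICC | 1 + 24 × ICC | 1.96 / √ | Formula | Mann-Whitney, simulated | t-test on school means, simulated |
|---|---|---|---|---|---|
| 0.02 | 1.48 | 1.611 | 10.7% | 10.6% | 5.8% |
| 0.05 | 2.20 | 1.321 | 18.6% | 16.1% | 4.3% |
| 0.10 | 3.40 | 1.063 | 28.8% | 24.0% | 4.4% |
| 0.20 | 5.80 | 0.814 | 41.6% | 38.9% | 4.2% |

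The simulated values are mostly lower because the ICC was placed on the underlying trait and item noise dilutes it in the observed score. With reliability 0.84, 0.20 × 0.84 = 0.168; then 1 + 24 × 0.168 = 5.03, 1.96 / √5.03 = 0.874, and the formula gives 38%, close to the simulated 38.9%. At ICC 0 the Mann-Whitney test rejected in 4.5%. That result and the last column show that the excess comes from ignoring school, not from the shape of the scores.

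**Step 3: the other school count.** The abstract gives eight schools per site, so 24 schools and 904 / 24 ≈ 38 children each. The same pair of calculations (simulated, then formula) gives 12–14%, 21–25%, 32–37% and 48–50% at the four ICCs.

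**The case against.** **Clustering is not said to be dropped.** A reader might infer that the non-parametric route discards school and that the self-perception p-values will therefore be invalid. The text does not support that. It names no method, rank and permutation methods that respect clusters exist, and the abstract promises multilevel approaches. What can be said is that no clustering provision is stated for that route. The error rates in step 2 apply only if a cluster-naive test is chosen. This objection stands.

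**The factor-score route is sound on clustering.** It puts the scores into the linear models, so the random intercepts and the mean differences with intervals remain. A CFA of the GPPP is planned anyway, and multivariate normality is a proper consideration when choosing a CFA estimator. This stands too. It does not explain why the same test should decide whether a mixed model is used at all, or which of the two routes is taken.

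**The error rates may be too high.** The plan itself calls 0.20 conservative, and it was chosen for the sample size, which rests on skill outcomes; no school-level ICC is given for the questionnaires. Schools are randomised within pairs ranked by socio-economic status, by site and schooling level, which could balance part of the between-school variance. A rank test on change scores could also have a different ICC. Hence the range, and its conditional status.

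**An analysis plan not shown may settle the choice.** A reader might also infer that the more favourable result will be picked. The article does not show that. Leaving a test unnamed would be ordinary condensation, but here the article itself commits to a data-dependent switch with an unresolved 'or'.

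**Conclusion.** The point holds in a limited form. The article fixes a gate that will almost always trigger, and then leaves two different analyses open with no rule for choosing. One keeps the clustering and the mean differences. The other has no stated clustering provision and, as an ordinary rank test, would give no mean difference with interval. Near-certain failure of the gate rests on the four-level items, the sample size and assumed item distributions, and it held under all three distributions tried. The type I error of about 11% to 42% for ICCs from 0.02 to 0.20 is what a test ignoring school would produce under unpaired randomisation of 36 schools; it is not a prediction of what the trial will do. Only the secondary questionnaire outcomes are affected. The Dragon Challenge primary outcome, physical activity and fitness are outside the rule. It should be corrected before the questionnaire data are analysed, but it does not threaten the main result.

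**What to change.** Replace the conditional sentence in Statistical analyses.

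- Remove the normality test as a gate.
- Name one outcome variable for each scale now: the scale score, or the CFA factor score with its estimator stated in advance.
- Analyse that variable in the linear mixed model the section already specifies (group, time and group-by-time, the stated covariates, and random intercepts for school, site and student). That is a repeated-measures model, and no change to a baseline-covariate model is needed for this point.
- If a check against non-normality is wanted, label it a sensitivity analysis and have it respect school as the unit of randomisation, for example a school-level permutation test that follows the pairing, or a cluster bootstrap interval.

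The cost is one rewritten sentence. No extra data, children or schools are needed.
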